#### Objective

The objective of aim 2 is to determine the association between identified digital biomarkers and cognitive function.

#### Overall Study Design of Aim 2

We will test the hypothesis that digital biomarker scores will negatively correlate with cognitive function scores. To test this hypothesis, we will conduct a pilot study using a new sample of 30 high school adolescents aged 14-15 years. After screening, consent, and baseline assessments, adolescents will play the *PlayForward* game. To validate the model developed in aim 1, the digital biomarkers identified in aim 1 will be extracted following completion of gameplay, and a digital biomarker score will be derived. We will then test the association between the computed digital biomarker score and cognitive function.

#### Participants and Source

Adolescents from 1 to 3 Connecticut high schools will be recruited. To be eligible for this study, participants must (1) attend a high school in Connecticut, (2) be aged between 14 and 15 years, (3) be willing to sit for 60 minutes per session to play the game, and (4) be able to provide assent and parental or guardian consent. Following screening, eligible adolescents who provide parental consent and assent will complete baseline assessments. Adolescents who complete baseline will be grouped into high-risk and low-risk groups based on their response to assessment of substance misuse, depression, and anxiety. High risk will be determined using their report at baseline of monthly use of any substance (alcohol, tobacco, marijuana, prescription drugs, inhalants, illegal drugs, and synthetic drugs), a score of >2 on the Patient Health Questionnaire-2 [58], and a score of >2 on the Generalized Anxiety Disorder 2-item scale [59]; low risk will be determined by no substance use in the past year, <2 on the Patient Health Questionnaire-2, and <2 on the Generalized Anxiety Disorder 2-item scale. We chose a higher age range (14-15 y) for aim 2 (in contrast to the age range of 11-14 y in aim 1) to ensure that we can recruit a high-risk sample (adolescents with substance misuse).

#### Recruitment and Informed Consent

This study will take place in high schools where the laboratory has established partnerships and has conducted trials in the past. Adolescents in participating high schools will be informed about this study. Adolescents who express interest will be provided a flyer with a QR code to complete a contact form if interested in participating in the study. Parents of interested adolescents who complete the contact form will be contacted to obtain parental permission. Following parental permission, adolescents will be screened for eligibility for participation in this study through a Qualtrics (Qualtrics) survey. Eligible adolescents will be asked to provide assent prior to enrollment into this study.

#### Data Collection and Storage

We will use Qualtrics, a web-based data collection software to obtain parental permission and adolescent assent, screen adolescents for study eligibility, obtain demographic information, and generate a study ID. Study IDs will be automatically generated after the adolescent has screened as eligible. PsyToolkit [60,61], an open source, web-based psychological instrument will be used to administer baseline assessments and conduct the tasks of cognitive function. PsyToolkit has been used in studies measuring working memory and response inhibition in adolescents [62,63] and has been shown to produce comparable results to tasks conducted in a laboratory [64]. Baseline assessment and task performance scores will be retrieved from the PsyToolkit website.

Gameplay data collection will be stored on iPads (Apple Inc) during gameplay. Following study completion, data for each participant will be retrieved from Qualtrics and PsyToolkit into a CSV file and merged by participant ID. Data from iPads will also be retrieved as log files. All retrieved data will be stored on secured data storage locations on the Yale server. Data collection will occur between April 2023 and February 2024.

#### Assessments and Cognitive Tasks

Table 2 [48,58,65-70] lists measures to be used for screening and administered at baseline. All listed measures have been validated among adolescents.

Table 3 [71-74] lists cognitive tasks to be completed by adolescents at baseline. All listed cognitive tasks have been validated among adolescents.

**Table 2 table2:** List of screening and baseline assessments for aim 2.

Construct	Name of questionnaire and reference	Number of items	Screening	Baseline
Demographics	Age, sex, and school name	—^a^	✓	—
Depression	Patient Health Questionnaire-2, Richardson et al [58]	2	✓	—
Anxiety	Generalized Anxiety Disorder-7, Bentley et al [65]	2	✓	—
Substance misuse	Screening to Brief Intervention scale, Levy et al [66]	7	—	✓
Substance use risk	Car, Relax, Alone, Forget, Friends, Trouble (CRAFFT) scale, Knight et al [70]	6	✓	—
Emotion regulation	Difficulties in Emotion Regulation Scale–Short Form, Kaufman et al [67]	18	—	✓
Cognitive function	Teenage Executive Function Inventory Scale, Thorell et al [68]	20	—	✓
Impulsivity	Urgency, Premeditation (lack of), Perseverance (lack of), Sensation Seeking, Positive Urgency, Impulsive Behavior scale, Pechorro et al [69]	20	—	✓
Self-efficacy to refuse drugs	Drug Use Resistance Self-Efficacy scale, Carpenter and Howard [48]	24	—	✓

^a^Not applicable.

**Table 3 table3:** Baseline cognitive tasks.

Construct or cognitive task and reference		Description	Metrics recorded
**Working memory**			
	n-back task, Pelegrina et al [71]	The 2-back task will be used. In the 2-back task, a series of letters will be shown to participants in a sequential order. Participants are to click a prespecified key on their device if the letter shown matches the letter shown 2 turns back.	Percentage of correct matches Percentage of missed matches Percentage of false alarms Mean response time
**Inhibitory control**			
	Go or no-go task, Bezdjian et al [72]	In the go or no-go task, participants are asked to click the spacebar when they see the “go” sign but do nothing when they see the “no-go” sign.	Response speed Number of errors Mean response time
	Stop-signal task, Kulendran et al [73]	In the stop signal task, 2 arrows, 1 pointing to the right and the other pointing to the left, will be shown in random order. In the first round, without the stop signal, the participant will click a prespecified key when the left pointing arrow is shown and a different prespecified key when the right pointing arrow is shown. In the second round which includes the stop signal, participants are to stop from clicking the arrows when the red signal appears.	Mean response time Error rate
**Selective attention, processing speed, and cognitive flexibility**			
	Stroop task, Stroop [74]	In the Stroop task, names of different colors (blue, green, yellow, and red) will be printed in either of the 4 colors. Participants are to use prespecified keyboard keys to identity the color in which the word is printed in and not the meaning of the word. If the word “yellow” is printed in green, the correct response would be to click on the key that corresponds to green.	Mean response time for congruent and incongruent stimuli

#### Study Setting and Study Flow

Figure 1 outlines study procedures. After obtaining verbal parental permission and adolescent assent, participants will be provided with their study ID to log-in to PsyToolkit to complete baseline procedures, which include 7 validated questionnaires and 4 performance-based cognitive tasks as described above.

Following the completion of baseline assessments or tasks, all enrolled participants will be provided a National Institutes of Mental Health–approved information sheet about the teen brain with resources on finding help. In addition, all participating schools have a school-based health center where students can seek help. Enrolled participants will use iPads to complete the entire *PlayForward* game over 6 to 7 sessions lasting 60 minutes each (the average number of 60-min sessions needed to complete the *PlayForward* game is 6). Gameplay sessions will occur 1 to 2 times/wk. The order in which the 4 cognitive tasks will be presented to participants will be random and generated by PsyToolkit. Adolescents will be compensated US $50 following the completion of baseline and US $70 after the completion of this study.

**Figure 1 figure1:**
[figure not shown]
Aim 2 procedures. CT: Connecticut.

### Statistical Analyses

#### Primary Outcomes

Working memory: the percentage of correct matches, percentage of missed matches, and percentage of false alarms from the 2-back task will be used to compute a working memory score.

Inhibitory control: the response speed and number of errors from the go or no-go task and average response time from the stop-signal task will be used to compute an inhibitory control score.

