#### Secondary Outcomes

Selective attention and processing speed: the average response time from the Stroop task will be used to compute the selective attention score.

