#### Planned Analyses

The model trained in aim 1 will be applied to the data collected in aim 2, and digital biomarker scores will be computed such that higher scores equate to higher risk for substance misuse. We will carry out a test of correlation (*r*) to determine the correlation between the digital biomarker score and (1) working memory score, (2) inhibitory control score, and (3) selective attention score.

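### The primary inhibitory control score takes two of its three parts from response speed, and its stop-signal part contains no measure of stopping

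*Protocol article*

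**What the plan says.** Under Statistical Analyses, Primary Outcomes, the inhibitory control score has three named inputs: "the response speed and number of errors from the go or no-go task and average response time from the stop-signal task". These "will be used to compute an inhibitory control score". Neither weights nor scoring direction are given.

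Table 3 describes the two tasks. In the go/no-go task participants "click the spacebar when they see the “go” sign but do nothing when they see the “no-go” sign". The stop-signal task has two rounds. "In the first round, without the stop signal, the participant will click a prespecified key when the left pointing arrow is shown", with a different key for the right arrow. In the second round "participants are to stop from clicking the arrows when the red signal appears". The metrics recorded for the stop-signal task are "Mean response time Error rate". No stop-signal delay or stop-signal reaction time appears anywhere in the article.

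Secondary Outcomes uses response time on another task for a different construct: "Selective attention and processing speed: the average response time from the Stroop task".

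Planned Analyses states the test: "We will carry out a test of correlation (*r*) to determine the correlation between the digital biomarker score and" each of the three cognitive scores. The Aim 2 design section expects these correlations to be negative.

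**The concern.** By the article's own task descriptions, successful inhibition is the absence of a press. It produces no response time. The stop-signal average response time can come only from arrows answered normally and from failed stops, and the first round is plain two-choice reaction time. The metric that could show failed stopping, the stop-signal error rate, is recorded but not used. Go/no-go response speed is likewise measured only on trials with a press. Go/no-go errors are therefore the only part of the score that can register failed inhibition directly.

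This matters because the score is one of the two primary outcomes of aim 2. Several candidate game metrics in Table 1 are completion or checking times, some mapped there to processing speed. A correlation could arise because slow players are also slow on the tasks, and it would be reported as inhibitory control. Conversely, a real relation with inhibition could be missed because it is diluted.

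**Working it through.** **1. The plan's own figure.** The Power section plans on r = 0.5, two-sided 0.05 and 80% power, with 29 participants. Fisher z: n = ((1.960 + 0.842)/atanh(0.5))² + 3 = (2.802/0.5493)² + 3 = 29.01. Power is 80.0% at n=29 and 81.4% at n=30. The figure reproduces, so the sample-size arithmetic is not in question. It does assume that r = 0.5 applies to the score actually analysed.

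**2. Share of speed in the score.** Assume three standardised parts with equal weights, errors uncorrelated with the speed parts, and correlation a between the two speed parts once both are scored in the same direction. Speed's share of the score variance is (2 + 2a)/(3 + 2a).
- a = 0: 2/3 = 67%
- a = 0.3: 2.6/3.6 = 72%
- a = 0.7: 3.4/4.4 = 77%

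Errors correlate with the score as strongly as speed does only when their weight is √(2 + 2a) against 1 for each speed part, a share of √(2 + 2a)/(√(2 + 2a) + 2).
- a = 0: 1.414/3.414 = 41%
- a = 0.7: 1.844/3.844 = 48%

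**3. Effect on the planned correlation.** The documents give no correlations between the parts, so the following are assumptions: equal weights; fast responding scored as good; errors load λ = 0.6-0.7 on inhibition; each speed part loads μ = 0.6-0.8 on a general speed factor; the two factors correlate φ; the biomarker correlates 0.5 with inhibition and is related to the task measures only through it.

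- Score variance: V = 3 + 2μ² + 4λμφ
- Correlation with inhibition: (λ + 2μφ)/√V
- Correlation with speed: (2μ + λφ)/√V
- Observed r = 0.5 × correlation with inhibition; power at n=30 from atanh(r) × √27 against 1.960

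With φ = 0:
- λ = 0.6, μ = 0.8: V = 4.28, √V = 2.069. Inhibition 0.6/2.069 = 0.29; speed 1.6/2.069 = 0.77; observed r 0.145; power 12%.
- λ = 0.7, μ = 0.6: V = 3.72, √V = 1.929. Inhibition 0.7/1.929 = 0.36; speed 1.2/1.929 = 0.62; observed r 0.18; power 16%.

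Over the whole range of λ and μ:

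| φ | Correlation with inhibition | Correlation with speed | Observed r | Power, n=30 |
|---|---|---|---|---|
| 0 | 0.29-0.36 | 0.62-0.77 | 0.15-0.18 | 12-16% |
| 0.3 | 0.47-0.53 | 0.68-0.81 | 0.24-0.27 | 24-29% |
| 0.5 | 0.57-0.65 | 0.71-0.84 | 0.28-0.32 | 33-41% |

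In each row the score correlates more with speed than with inhibition.

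**4. Comparison.** A score from two inhibition indicators (go/no-go errors and stop failures, each loading λ and otherwise independent) correlates 2λ/√(2 + 2λ²) with inhibition.
- λ = 0.6: 1.2/√2.72 = 0.73; observed r 0.36; power 51%
- λ = 0.7: 1.4/√2.98 = 0.81; observed r 0.41; power 61%

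This too falls short of 80%, but it is better than any case in the table.

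**The case against.** The strongest reply is that no equal-weight score is planned. The article names the ingredients only, and weights, standardisation and polarity are details that an article may leave to a fuller document. That stands. A reader might infer that the score mostly ranks motor speed; the text does not establish this. With errors and speeds uncorrelated, speed would cease to dominate if errors carried about 41-48% of the weight or more. The arrow task is also a two-choice response, so its response time includes decision time and caution as well as movement. General response speed is the accurate term.

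A reader might also see a fault in response speed and response time running in opposite directions, or infer that fast, impulsive pressing will be rewarded. Reversing a metric when scoring is routine, and the article does not say which direction counts as good. This is a reason to state the direction, not an error in itself.

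The size of the loss depends on assuming that speed and inhibition are unrelated. If they are positively related, the loss is smaller, as the table shows.

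Finally, this is a proof-of-concept study with 30 participants, go/no-go errors do remain in the score, and the working memory outcome is unaffected. The limitations section concedes that the game metrics may represent inhibitory control poorly, but that concerns the game, not the reference score.

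None of this restores the stop-signal part. Under any weighting, it contributes a response time from a task in which success leaves none, while the recorded error rate is set aside.

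**Conclusion.** The point holds as a construct-validity weakness in a stated scoring rule for a primary outcome. Two of three parts are speeds, the stop-signal part has no stopping measure, and an available metric that could supply one is omitted; these facts are in the text. That the score would reflect general response speed more than inhibition is conditional on equal or near-equal weights.

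The size is illustrative. Under the assumptions above, power at n=30 for a true correlation of 0.5 with inhibition is 12-16% if speed and inhibition are unrelated, and about 24-41% if they correlate 0.3-0.5, against the 80% planned. The documents do not support the stronger conclusions that the score holds no information on inhibition or that the sample-size calculation is wrong. This should be fixed, with medium confidence in the size.

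**What to change.** Before aim 2 is analysed:

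- Replace the stop-signal mean response time with a stopping measure. If stop delays are fixed and the PsyToolkit output separates the trials, use the failure rate on second-round stop trials; if it does not separate them, use the recorded overall error rate. If delays are adaptive and stored, use stop-signal reaction time.
- Take go/no-go response speed out of the inhibitory control score and report both speeds as processing speed.
- State the direction and weights of the remaining parts.

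The article says that aim 2 analysis starts only after data collection ends, so this can be specified in advance and needs no new task. It may not be free. Table 3 lists a single error rate, not split by round or trial type and possibly including wrong-arrow presses, so trial-level output may have to be retrieved. The article does not say whether delays are fixed or adaptive; adaptive delays would hold the failure rate near a constant, and it would not separate participants. Even with fixed delays, the failure rate is coarse when stop trials are few.

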#### Secondary Outcomes

Selective attention and processing speed: the average response time from the Stroop task will be used to compute the selective attention score.

#### Predictors

In-game performance metrics extracted in aim 1 will also be extracted in aim 2. We will test if specific in-game performance metrics are predictive of cognitive function (working memory and inhibitory control) measured by performance-based tasks in a sample of adolescents (n=30).

#### Planned Analyses

The model trained in aim 1 will be applied to the data collected in aim 2, and digital biomarker scores will be computed such that higher scores equate to higher risk for substance misuse. We will carry out a test of correlation (*r*) to determine the correlation between the digital biomarker score and (1) working memory score, (2) inhibitory control score, and (3) selective attention score.

#### Power

With an expected moderate correlation of 0.5 between in-game performance score and validated measures of cognitive function [28], a total of 29 participants will provide 80% power at the .05 2-sided significance level. A larger sample size will yield conventional levels of statistical significance for lower correlation coefficients (n=30 for *r*=0.5 and n=47 for *r*=0.4). For this pilot project, we anticipate a correlation of 0.5 based on prior validation studies comparing game-based cognitive assessment to standardized assessment [75-77].

### Ethical Considerations

The Yale institutional review board approved this study and its procedures on October 11, 2022 (IRB #2000033084). This study is covered by a Certificate of Confidentiality from the National Institutes of Health. Given the sensitive nature of this study, a Health Insurance Portability and Accountability Act waiver and waiver of written parental consent was obtained.

## Results

This study was funded by the National Institute on Drug Abuse through the Center for Technology and Behavioral Health at Dartmouth Pilot Core in May 2022. For aim 1, we completed cleaning of in-game log files in preparation for data extraction. In total, 166 log files were initially available for data extraction. Following data cleaning, 6 files were excluded for reasons such as the data storage files were corrupted, the data structure of log files was different from the rest of the files, and it was impossible to determine the reason for this difference. As such, a final sample of 160 is being used for analysis. The number of extracted in-game performance metrics is 285 (Multimedia Appendix 1). The R software [46] was used in extracting metrics from game log files, and codes are being stored on GitHub. Analyses are currently underway. For aim 2, data collection is ongoing and is projected to end in February 2024. Currently, we have enrolled 12 participants. Data analysis for aim 2 will begin once data collection is completed. The results from both aims will be reported in a subsequent publication, which we expect to publish in the winter of 2024.

## Discussion

Adolescent substance misuse is a predominant public health problem. However, most adolescents at risk for substance misuse are not identified early [78]. Early identification of high-risk adolescents can inform the delivery of targeted interventions that prevent the development of negative outcomes. However, identifying adolescents at risk for substance misuse is not routinely done due to a myriad of factors. Although mobile phones and wearable devices have been used to identify and measure digital biomarkers for health outcomes [24-27], the use of games is less widely studied. The use of game-based assessment for mental health purposes has been on the rise and may be used to capture potential biomarkers of health outcomes that can be used for screening and monitoring [22]. The use of games for risk identification offers a promising solution as these can be deployed without the need for provider supervision, can offer privacy to the adolescent completing the game-based screener, and has benefits over self-report data as it would provide a more objective assessment of risk.

In this proof-of-concept study, we will test the utility of in-game performance metrics—digital biomarkers—to identify adolescents at risk for substance misuse. We will also test the hypothesis that adolescents with poor cognitive function will perform worse in the game and be at higher risk for substance misuse. We will be assessing aspects of cognitive function that are implicated in the development of substance misuse and impacted by substance misuse. We build on prior studies that have successfully used game metrics to measure cognitive function [38,40] and extend prior knowledge in the field by applying it to substance misuse. Games offer an engaging way to assess a wide range of factors among adolescents, most of whom play games [17]. This study has several strengths. To the best of our knowledge, we will be the first to test the utility of in-game performance metrics to be used as digital biomarkers of substance misuse. We will also be the first to investigate game-based digital biomarkers in an adolescent population.

This study has several limitations. We are using a game that was not initially designed to measure cognitive function. As such, the game metrics may be poor representations of working memory and inhibitory control. However, other studies have demonstrated that performance metrics collected in a game could be useful in predicting cognitive functions [38,40]. We are using a game that is designed to change behavior related to substance use risk. As such, this game may not be ideal as an assessment tool since the tools’ predictive ability may wane with repeated use in the setting of positive behavior change. However, other studies have documented that even games designed primarily for assessment can change cognitive processes in ways that can threaten the validity of the game-based tool [79,80]. We chose to use this game-based intervention due to the availability of existing data for this proof-of-concept study, which, if successful, will provide preliminary data for future development of a game-based assessment tool for substance misuse risk. Another limitation is that the initial sample on which the prediction model will be trained has a low prevalence of substance misuse. This imbalance may limit the performance of the prediction models to predict substance misuse. To address this, we will use data augmentation methods such as Synthetic Minority Oversampling Technique [81]. In addition, our eligibility criteria for aim 2 will allow us to recruit a sample of adolescents with higher risk for substance use than in aim 1, which may enhance the performance of the model.

Despite limitations, this study represents a novel and likely highly impactful examination of the use of digital games as not only interventions but also potentially as screening and data collection tools. If found to be successful in predicting substance use, it will inform the future design of game-based assessment tools for substance misuse risk. With their broad level of reach and high engagement, games could seamlessly provide data on adolescent substance misuse risk and help to close the gap in screening and early intervention, leading to improved health outcomes in adolescents.

